## Abstract

**Methods::**

A randomized, prospective, double-blind (patient and evaluator) clinical trial. The participants (n = 60) will be randomly distributed into 2 groups. The experimental group will receive a sublingual Immunotherapy for 3 months. The control group will receive the mometasone furoate nasal spray for 3 months. Before treatment, 1 month and 3 months after treatment, total nasal symptom score scale, Visual analogue Scale and Quality of Life questionnaire of rhinoconjunctivitis will be measured and Changes of the serums of IgE, interferon-γ, IL-4, IL-17, tumor necrosis factor-α, IL-5, IL-9, IL-13, IL-25, IL-33, vascular endothelial growth factor, TSLP and IL-22 in both groups. The measurements will be performed by the same researcher who was unaware of the participants’ subgroup.

**Discussion::**

We believe that the treatment of perennial AR with sublingual Immunotherapy and nasal hormones will be more effective in these patients. Furthermore, the sublingual Immunotherapy mainly acts mostly on the cellular immunity, while nasal hormones mainly act on local inflammatory responses. We expect to clarify which treatments are more effective and how they work in improving perennial AR.

## 1. Introduction

Allergic rhinitis (AR) is a common and frequent ailment of otolaryngology. It is a perennial or seasonal disease with symptoms such as sneezing, runny nose, itching nose, nasal congestion and anosmia.^[1]^ Numerous epidemiological studies have been shown that AR affects 10% to 40% of the global population.^[2]^ It has become a major chronic inflammatory respiratory disease and is considered 1 of the most difficult diseases to treat globally.^[3]^

Although AR is not a serious disease, but due to its recurrent, persistent, and complicating characteristics,^[4–6]^ it has a serious impact on the quality of life and socio-economic well-being of patients and has become a major global health problem.^[7]^ It is reported that economic losses in EU countries can be between 30 and 50 billion euros per year.^[8]^ A large sample study in the United States showed that AR reduced worker productivity more than any other disease, including hypertension, diabetes, and heart disease.^[9]^

The treatment of AR mainly includes environmental control, drug therapy, immunotherapy, etc.^[9,10]^ all kinds of treatment methods have their advantages. However, there are no good measures to avoid dust mite allergy at present. Therefore, it is becoming more and more important for scholars to change patients’ allergic physique through specific immunotherapies.

AR is a noninfectious chronic inflammatory disease of the nasal mucosa mainly mediated by immunoglobulin E after exposure to allergens in atopic individuals.^[11]^ Regulating the immune balance of Th1/Th2/Th17 cells during the occurrence and development of AR is considered to be an important approach in the current treatment of AR. But there is increasing evidence that innate immune response is also the pathogenesis of AR. Innate lymphoid cells (ILCs) are involved in mucosal immune formation, lymphocyte development, tissue damage repair and epithelial barrier protection, and play an important role in fighting infection, regulating inflammation and maintaining immune homeostasis. Some studies have proposed that the 3 subsets of innate lymphocytes (ILC1s, ILC2s, ILC3s) are functionally approximately corresponding to Th1, Th2, and Th17 of T helper cells. However, current studies have not been conclusive, and the specific mechanism of ILCs in the development of AR has not been fully elucidated.

Our objective was to compare the efficacy of sublingual immunotherapy and nasal hormone in the treatment of perennial AR and the mechanism of action on ILCs, and to reveal the correlation between ILCs (ILC1s, ILC2s, ILC3s) and Th1/Th2/Th17 cell immunity, so as to provide research basis for clinical study of AR.

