### 2.4. Variables studied

The recruiting physician (PhD in otolaryngology with 8 years of experience in the field) will perform all assessments for the study and remain blinded to the group to which subjects are assigned at all times.

Table 1 shows the sociodemographic variables and the values that each 1 may have. The following variables: sex, age, occupation, contact information, duration of symptoms, allergic history and Genetic history will be recorded at the beginning of treatment by anamnesis.

**Table 1 T1:** Independent sociodemographic variables.

Variable	Values
Sex	Man/Woman
Age	Years
Occupation	What kind of job
Contact information	Phone number
Duration of symptoms	Daily – Weekly – Monthly – Quarterly – Annual
Allergic history	Yes/No
Genetic history	Yes/No

Table 2 shows the outcome variables, the evaluation period for each variable, and the measurement tools used. All assessments will be performed by a physician, who will also be responsible for recruitment, and the group assigned to each subject will be assessed in a blinded manner throughout the assessment period.

**Table 2 T2:** Outcome variables, the evaluation period for each variable.

Outcome variables	Evaluation period			Measuring instrument
	Baseline	1 mo post-treatment		3 mo post-treatment
Nasal symptoms and signs score	X	X	X	TNSS
Intensity of nasal pain (main symptom)	X	X	X	VAS
Rhinitis Quality of Life Questionnaire	X	X	X	RQLQ
Serological test	X	X	X	The level of serological indicators

RQLQ = rhinoconjunctivitis quality of life questionnaire, TNSS = the total nasal symptom score, VAS = Visual analog scale.

The primary outcome indicator is the decrease in the total nasal symptom score^[14]^ (including self-assessment of nasal congestion, runny nose, itchy nose, and sneezing) and Changes in the level of serological indicators (Enzyme-linked immunosorbent assay will be used to detect). The secondary outcome indicators are visual analogue scale and Standardized Rhinoconjunctivitis Quality of Life Questionnaire^[15]^ and mitigate changes in drug use. Data will be recorded by Case report forms (CRFs) before treatment, at 1 month of treatment, and at 3 months of treatment.

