## 3. Discussion

AR is a noninfectious chronic inflammatory disease of nasal mucosa mainly mediated by immunoglobulin E after atopic individuals are exposed to allergens. AR can be classified as seasonal or perennial according to the type of allergen. According to the course of disease can be divided into intermittent and persistent; The impact on quality of life is divided into mild and moderate-severe.^[1]^ Current studies have shown that Th1/Th2/Th17 cell immune imbalance is an important mechanism of AR pathogenesis.^[16–18]^

In the development of AR, T cells are the only cells that react directly with antigens. Helper T cells are derived from interleukin-2-producing precursor cells. After initial stimulation, these cells develop into Th0 cells (CD4 + T cells), which produce cytokines including IFN-γ, IL-2, IL-4, and IL-5. Th0 cells differentiate into Th1 cells under the induction of IL-12 and IFN-γ, which secrete IFN-γ, IL-2 and tumor necrosis factor-β and participate in cellular immune response. Under the induction of IL-4, they differentiate into Th2 cells and secrete IL-4, IL-5, IL-13, IL-8 and other cytokines to participate in humoral immune response.^[19]^ Th17 is a new type of T helper lymphocyte, which is a pro-inflammatory cell that can activate the body’s inflammatory response and participate in the regulation of the autoimmune system. It was discovered in 2003 and got its name because it can secrete iconic factors such as IL-17 and IL-23, and plays an important role in the body’s self-immune response.^[20]^

In the occurrence and development of AR, IFN-γ, IL-4 and IL-17 are the main effectors of Th1, Th2 and Th17 respectively.^[21]^ It has been reported^[22]^ that IL-4 immune inflammatory factor released by Th2 cells has a regulatory effect on the level of IgE. However, IFN-γ released by Th1 cells has an inhibitory effect on IL-4 secretion by Th2 cells.^[23]^ IL-17 is a cytokine secreted by Th17 cells with strong proinflammatory effect. Serum IL-17 in patients is positively correlated with IgE level, and its increased level can be used as an indicator for the diagnosis of AR.^[24]^ Therefore, regulating the immune balance of Th1/Th2/Th17 cells is an important way to treat AR. However, increasing evidence shows that innate immune response is also the pathogenesis of AR.

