The innate immune system is the first line of defense against invading pathogens or antigens, and its response is rapid and nonspecific. Subsequently, the activated adaptive immune system performs complete elimination of specific antigens.^[25]^ ILCs, as an important effector cell population of innate immunity, are characterized by 3 major characteristics: they do not undergo receptor gene rearrangement and clonal selection, lack of phenotypic markers of myeloid cells and dendritic cells, and their morphology belongs to the lymphoid lineage. ILCs are mostly tissue-resident lymphocytes, mainly distributed in the tonsil, broncho-lung, intestinal tract, skin and other mucosal barrier sites. Ilcs are involved in mucosal immune formation, lymphocyte development, tissue damage repair and epithelial barrier protection, and play an important role in fighting infection, regulating inflammation and maintaining immune homeostasis.^[26]^

According to the phenotype and cytokines secreted by ILCs, ILCs can be divided into 3 subsets of type 1, 2 and 3 innate lymphocytes (ILC1s, ILC2s and ILC3s),^[27]^ which are functionally approximately corresponding to Th1, Th2 and Th17 of Helper T cells. ILC1s includes natural killer cells (NK) and ILC1 cells, which depend on T-box transcription factor and produce large amounts of IFN-γ and tumor necrosis factor-α. The development of ILC2s depends on the transcription factor GATA3 to produce Th2-type cytokines and other effector molecules, such as IL-4, IL-5, IL-9, IL-13 and Vascular endothelial growth factor, which drive the development of type 2 immune response. Moreover, unlike T cells, which recognize specific antigens, ILC2s respond to nonspecific cytokines, including IL-25, IL-33, and Thymic stromal lymphocytes produce hormone. TSLP can stimulate the activation and proliferation of ILC2s to produce a large amount of IL-5 and IL-13, resulting in airway inflammation and airway hyperresponsiveness. ILC3s depend on the transcription factor RORTt to produce cytokines IL-17 and IL-22 similar to Th17.^[27–29]^

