Some studies have found that after the nasal epithelium of AR patients is stimulated by allergens, the pro-inflammatory cytokines in the epithelium increase, and IL-25, IL-33 and TSLP can be detected in the nasal lavage fluid of patients with house dust mite allergy.^[30,31]^ However, the level of IL-25 released by peripheral blood mononuclear cells will be up-regulated after basophils of birch and pollen allergy patients are stimulated by allergens.^[32]^ Other studies have shown that the number of ILC2 in peripheral blood of patients with house dust mite allergy is increased, and its number change is positively correlated with the severity of symptoms.^[33,34]^ Studies on AR caused by plant allergens found that during the grass pollen season, the number of ILC2 and ILC3 in peripheral blood of patients with grass pollen allergy increased, while the number of ILC1 did not change significantly.^[35]^ However, Bartemes et al^[36]^found that the number of ILC2 in peripheral blood of AR patients did not increase, but that of asthma patients increased. There is no consensus on whether the number of ILC2s in peripheral blood of AR patients is increased.

In conclusion, the mechanism of AR is mainly related to the imbalance of Th1/Th2/Th17 cell immunity, but more and more evidence shows that innate immune response is also the pathogenesis of AR, and the specific mechanism of ILCs in the development of AR has not been fully elucidated.

Therefore, this study aims to explore the efficacy of sublingual desensitization in the treatment of perennial AR and its mechanism of action on ILCs, reveal the correlation between ILCs (ILC1s, ILC2s, ILC3s) and Th1/Th2/Th17 cell immunity, and provide research basis for clinical research on AR.

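### The aims on ILCs and their correlation with Th1/Th2/Th17 immunity do not match the listed outcomes, which contain serum proteins but no cell measure

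*Protocol article*

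**What the plan says.** Section 1 (Introduction) gives two aims beyond efficacy: "the mechanism of action on ILCs, and to reveal the correlation between ILCs (ILC1s, ILC2s, ILC3s) and Th1/Th2/Th17 cell immunity". The close of section 3 (Discussion) restates the second of them: "reveal the correlation between ILCs (ILC1s, ILC2s, ILC3s) and Th1/Th2/Th17 cell immunity, and provide research basis for clinical research on AR".

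On measurement, the Abstract (Methods) lists "Changes of the serums of IgE, interferon-γ, IL-4, IL-17, tumor necrosis factor-α, IL-5, IL-9, IL-13, IL-25, IL-33, vascular endothelial growth factor, TSLP and IL-22". Section 2.4 makes part of the primary outcome "Changes in the level of serological indicators (Enzyme-linked immunosorbent assay will be used to detect"), next to the nasal symptom score. Table 2 has four outcome rows: TNSS, VAS, RQLQ and a serological test, whose instrument is given as "The level of serological indicators".

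On biology, section 3 says that "IFN-γ, IL-4 and IL-17 are the main effectors of Th1, Th2 and Th17 respectively", and names IL-5 and IL-13 as further Th2 products. The same section assigns products to ILC1s, ILC2s and ILC3s, including the statement that "ILC3s depend on the transcription factor RORTt to produce cytokines IL-17 and IL-22 similar to Th17". It also says that ILCs are found mainly in tissue, and it describes previous studies that counted ILC subsets in blood.

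The Abstract (Discussion) expects immunotherapy to work mainly through cellular immunity, while "nasal hormones mainly act on local inflammatory responses".

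**The concern.** The aims concern cell populations, but the listed measurements are concentrations of proteins in serum. A serum concentration does not show which cell secreted the protein. That gap matters more here because the article itself credits the same proteins to both cell families. A rise or fall in IL-4, for example, could come from Th2 cells, ILC2s or both.

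At stake is what the trial may conclude. Serological change is part of the primary outcome, so these data will be prominent in the report. Read against the stated aims, a serum change could be reported as an effect on ILCs, and a correlation among serum proteins as evidence that ILC and Th immunity are linked. Neither inference would be supported. The same holds for the expected contrast between cellular and local action, if it is presented as something that serum levels can test.

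**Working it through.** There is no sample size, power or alpha figure behind this point, so there is nothing of the plan's own to reproduce. The check compares two lists.

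**Inputs.** The 13 measured proteins come from the Abstract (Methods). The products of each cell type come from section 3. Only measured proteins are kept below; IL-2, TNF-β, IL-8 and IL-23 are named as Th products but not measured.

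| Pair | Th products measured | ILC products measured | Shared |
|---|---|---|---|
| Th1 / ILC1 | IFN-γ | IFN-γ, TNF-α | IFN-γ |
| Th2 / ILC2 | IL-4, IL-5, IL-13 | IL-4, IL-5, IL-9, IL-13, VEGF | IL-4, IL-5, IL-13 |
| Th17 / ILC3 | IL-17 | IL-17, IL-22 | IL-17 |

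**Counts.**
- Th products measured: 1 + 3 + 1 = 5.
- ILC products measured: 2 + 5 + 2 = 9.
- Shared: 1 + 3 + 1 = 5, so Th-only is 5 − 5 = 0 and ILC-only is 9 − 5 = 4 (TNF-α, IL-9, VEGF, IL-22).
- In neither list: 13 − 9 = 4 (IgE, and IL-25, IL-33 and TSLP, which the article describes as signals acting on ILC2s).
- Cell counts or phenotypes among the 13: 0.

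The overlap is complete from the Th side (5 of 5) and partial from the ILC side (5 of 9). The phrase on IL-22 could be read as making it a Th17 product too. The counts then become 6 of 6 and 6 of 9, and there is still no Th-only marker.

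**Consequence for a correlation.** The article defines no ILC score, no Th score and no pairing of markers. As an illustration only, assume equal-weight sums of standardised, mutually uncorrelated proteins. If the Th score has *a* components, the ILC score *b*, and *k* are common to both, the correlation forced by the overlap is r = k / √(a × b).

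- Th1 with ILC1: 1 / √(1 × 2) = 0.71.
- Th2 with ILC2: 3 / √(3 × 5) = 0.77. With IL-4 alone for Th2: 1 / √(1 × 5) = 0.45.
- Th17 with ILC3: 1 / √(1 × 2) = 0.71.
- The same single protein on both sides: 1 / √(1 × 1) = 1.
- No protein in common, for example IFN-γ against TNF-α: 0 / √(1 × 1) = 0.

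The forced part thus runs from 0 to 1 according to a choice that the article does not make. Even where it is 0 the aim is not met: in the last example the IFN-γ may itself come from ILC1s, so the result is a correlation between two serum proteins, not between two cell families.

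**The case against.** Several points can be made for the plan, and some of them stand.

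- *The article is condensed and its Figure 1 is not shown, so a cell assay or a nasal sample may exist elsewhere.* This stands as a limit. A reader might infer that no nasal sample is taken; the article supports only that no nasal or cell outcome is listed. It does not remove the mismatch, because the article sets out its outcomes, instruments, proteins and assay in full. An analysis plan can choose a correlation method but cannot supply cell data that were not collected.
- *Nothing says that the same protein will be used on both sides.* This stands. A reader might infer that each ILC-Th correlation will equal exactly 1, or be strong by construction. With no scores or pairings defined, that is not established; inflation is possible, not certain.
- *Four proteins are named only as ILC products, and three more act on ILC2s.* True, but none shows cell origin in serum, and there is no Th-only marker to correlate them with.
- *The serum comparison is a sound randomised contrast.* This stands. The change in each marker between arms is well defined. A reader might infer that the serum outcome has no valid estimand; what fails is the attribution to a cell type and the correlation aim.
- *The cellular-versus-local sentence is a belief stated before results.* This stands. It is an expectation and needs no deletion as a conclusion, only a limit on how it is used later.

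**Conclusion.** The stated aims on ILCs do not match the listed outcomes. Of the 13 laboratory measures, none is a cell measure, and every measured Th product (5 of 5) is also credited to ILCs by the article itself. The mechanism of action on ILCs and the ILC-Th correlation are not identifiable from these data. A computed correlation could be inflated by shared proteins, by an amount that depends on an undefined pairing.

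This rests on two assumptions: that the outcomes in the Abstract, section 2.4 and Table 2 are the complete laboratory outcomes, and that section 3 gives the marker assignments that the investigators would use. The 0.45 to 0.77 figures are illustrations under invented scores, not predictions. The comparisons of symptoms, quality of life and each serum marker between arms stand as they are.

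**What to change.** 1. In the Introduction and at the end of the Discussion, replace the mechanistic aim with wording such as: *to compare between arms the changes in the listed serum markers (IgE, the cytokines, VEGF, IL-25, IL-33 and TSLP)*. Keep its status consistent with section 2.4, where serological change is part of the primary outcome. Calling it exploratory in the aims alone would create a new contradiction.
2. Drop the correlation between ILCs and Th1/Th2/Th17 as an aim.
3. State that changes in serum markers will not be attributed to ILCs or to Th cells.
4. Do not present the cellular-versus-local expectation in the Abstract as something that these serum data can test.
5. If the full protocol contains a cell-level measure of ILC and Th subsets, list it as an outcome in section 2.4 and Table 2 and tie the ILC aim to it in place of steps 1 and 2. An investigator who wishes to keep the aim without such a measure would have to add one before sampling starts, since cell data cannot be recovered from serum.

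Steps 1 to 4 cost only wording and need no new assay. The trial gives up a mechanistic claim that its listed measurements cannot support.

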## 2. Methods

### 2.1. Study design

A randomized, prospective, double-blind (patient and evaluator) clinical trial. The Researchers should not be blinded due to the use of therapeutic method. Figure 1 shows a diagram with the different phases of the study.

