### 2.2. Study population. Sample recruitment

We will recruit and include 60 participants with perennial AR from the outpatient Department of Otorhinolaryngology Head and Neck Surgery Sant by the People’s Hospital of Anshun City of Guizhou Province (China). All participants receiving this service must be seen by a physician (allergy subspecialist or general physician). All those diagnosed with perennial AR (of more than 1 years duration) according to the Guidelines for AR^[1,12,13]^ during that appointment will be referred to a Outpatient physician of otolaryngology Head and neck Surgery, who will check whether they meet the other inclusion and exclusion criteria before offering them the opportunity to participate in the study.

The inclusion criteria will be: We will include participants with perennial AR only (not seasonal AR); above 18 years old to below 65 years old; both sexes; The participants has not received specific immunotherapy in the past 1 month or has not used any drugs to treatment the AR in the past 1 week; The participants must be examined with a positive result in the IgE sensitization test to aeroallergens (skin prick test or serum allergen specific IgE); they must with normal cognitive function and agree to participate in this study and sign the informed consent form.

The exclusion criteria will be: Participants who met any of the following criteria were excluded: The participants with severe nasal septum deviation, chronic rhinosinusitis, bronchial asthma, nasal polyps, upper respiratory tract infection, lung infection and other diseases; with severe dysfunction of heart, liver, kidney or autoimmune diseases; Pregnant or lactating women; Allergic constitution and allergic to the experimental drugs and ingredients; With drug addiction history; With major neuropsychiatric diseases who cannot take medication regularly; participating in other clinical trials.

The participants who meet all inclusion criteria and not meet exclusion criteria will have the opportunity to participate in the study and provide all relevant information orally and in writing. They will be told to be randomly assigned to study groups, each of which will be treated with a different drug, all of which are appropriate for their condition, and the goal of the study is to determine which drug produces the best results.

To maintain this blindness, the participants will not be told which group they had been assigned to.

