### 2.3. Randomization

We will be collected 60 subjects and randomize them into 2 groups (the experimental group and control group.) and use a computerized randomization method using EXCEL software and RAND function to generate random numbers (a total of 60 random numbers). Sixty randomly selected subjects will have a 1/2 chance of being randomly assigned to either the experimental or control groups. According to the order of presentation, participants will be assigned to the corresponding group for treatment according to the generated random number table.

The ENT clinic practitioner performing the intervention will be the only 1 with access to the list generated by the computer program. This physician cannot be blinded by using manual techniques, and he/she will know which group the subject is assigned to by referring to the number assigned by the evaluator.

To ensure the concealment and blindness of the task, the subjects will not know which group they have been assigned to.

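### The trial is called patient-blind, but the only blinding method stated cannot hide a sublingual product from a nasal spray, so as written the self-rated symptom score is unblinded

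*Protocol article*

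**What the plan says.** The Abstract and section 2.1 of the protocol article both give the design as "A randomized, prospective, double-blind (patient and evaluator) clinical trial". Section 2.1 adds that the researchers are not blinded because of the nature of the treatments, and section 2.3 says the same of the clinic practitioner who delivers them.

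The Abstract sets out the two arms: "The experimental group will receive a sublingual Immunotherapy for 3 months. The control group will receive the mometasone furoate nasal spray for 3 months".

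Section 2.2 says participants will hear that they are "randomly assigned to study groups, each of which will be treated with a different drug". It then says that blinding is kept by not telling them their group. Section 2.3 repeats the idea: "To ensure the concealment and blindness of the task, the subjects will not know which group they have been assigned to". No other means of blinding patients appears.

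Section 2.4 names two primary components. The first is the fall in TNSS, described as "including self-assessment of nasal congestion, runny nose, itchy nose, and sneezing". The second is the change in serological indicators measured by ELISA. VAS and RQLQ are secondary. One physician recruits, performs all assessments and is said to stay blinded throughout.

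**The concern.** A design described as patient-blind should contain something that stops patients from recognising their treatment. Here the two treatments enter by different routes, and the stated safeguard is silence about the group name. A patient who is given a spray knows it is a spray.

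This matters most for a self-rated score, where the patient is the assessor. A blinded physician who collects TNSS is recording the judgement of someone who knows the treatment. VAS and RQLQ are open to the same effect. The evaluator's own blinding is also at risk, since one remark from a patient about a spray or a sublingual product discloses the arm.

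The practical stake is the label. A report that repeats the words double-blind would credit the symptom comparison with a protection from expectation bias that the described procedures do not provide. TNSS is the primary clinical measure of efficacy, and comparing efficacy is the stated objective.

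**Working it through.** **1. Setting the statements side by side**

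| Element | What the article gives | Where |
|---|---|---|
| Claim | Patient and evaluator blinded | Abstract; 2.1 |
| Experimental arm | Sublingual route | Abstract |
| Control arm | Nasal spray | Abstract |
| Told to patients | Each group has a different drug | 2.2 |
| Method of patient blinding | Group not disclosed | 2.2; 2.3 |
| Placebo, dummy or other masking | None described | – |
| Rater of TNSS | The patient | 2.4 |
| Serology | ELISA, a laboratory measurement | 2.4 |

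If the arms are as described, the route is visible at the first administration and differs between arms. Non-disclosure of the group name does not alter that. The claim and the stated method therefore cannot both stand. This is a conflict within the article and not merely a detail left out, because the article does say how patient blinding is maintained.

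**2. Which outcomes are affected**

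- TNSS: directly, because section 2.4 calls it a self-assessment.
- VAS and RQLQ: in the same way, on the reading that a symptom-intensity scale and a quality-of-life questionnaire are answered by the patient. Section 2.4 uses the word self-assessment only for TNSS.
- ELISA serology: much less, since a patient's expectation does not enter the reading of the assay. No coding of samples is described.

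**3. Illustration of size**

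The article has no figure to reproduce: it states no SD, significance level, test or expected bias. Every input below is an assumption.

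- Per arm: n = 30, from 60 participants with a 1/2 chance of each group. Section 2.3 does not guarantee an exact 30:30 split.
- Test: two-sample t-test, two-sided 0.05, 58 degrees of freedom, critical value 2.00.
- True difference: zero. Spurious difference between arms from unblinded rating: b SD, in either direction.
- Noncentrality = b / √(2/30) = b / 0.258. The chance of a significant result is the probability that the noncentral t falls beyond ±2.00.

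| b (SD) | Noncentrality | Chance of a significant TNSS difference |
|---|---|---|
| 0 | 0 | 5.0% |
| 0.1 | 0.39 | 6.7% |
| 0.2 | 0.77 | 11.9% |
| 0.3 | 1.16 | 20.8% |
| 0.4 | 1.55 | 33.2% |

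A normal approximation gives 6.7%, 12.1%, 21.3% and 34.1% for 0.1 to 0.4 SD, so the choice of method matters little.

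**The case against.** The strongest reply is that this is a condensed article. It has no section describing the interventions, its flow diagram is not shown, and nowhere does it say that placebos are absent. A reader might infer that no dummy exists and that every participant will certainly know the arm. The documents do not support that: the absence of a dummy is an inference, and a fuller protocol could describe one. What survives is narrower. The article states a method, that method cannot hide two routes, and no other is offered.

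A second stronger reading is that the whole primary outcome is open-label. That does not hold either, because ELISA serology is also primary and is much less exposed.

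A third is that expectation will favour immunotherapy. Both arms are active, and participants are told that the drugs are ones "each of which will be treated with a different drug, all of which are appropriate for their condition". Knowing one's route does not show which arm a patient expects to do better. Bias could run in either direction or be negligible, and the table above cannot be read as an estimate of this trial's false-positive rate.

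Finally, relabelling does not reduce expectation bias in TNSS. That is true. It corrects the claim made for the result, and the other safeguards protect the evaluator and the laboratory.

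**Conclusion.** The point stands in this form: as written, the patient-blinding claim is contradicted by the article's own description of the arms and of how blinding is kept. It applies to the self-assessed TNSS and to the patient-reported VAS and RQLQ. It does not extend in the same degree to serology. Evaluator blinding is possible but fragile.

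The conclusion rests on the text alone and needs no calculation. The illustrative range, 5% with no bias to about 33% at 0.4 SD, shows only how sensitive a comparison of about 30 per arm would be. The direction and size of any bias are unknown. The label must be corrected, or the missing masking described, before results are reported as double-blind.

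**What to change.** There are two ways to resolve the conflict.

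1. If a double-dummy already exists, describe it and amend the blinding sentences in sections 2.2 and 2.3 so that they no longer rest on non-disclosure alone.
2. Otherwise, replace the design label in the Abstract and section 2.1, and the blinding sentences in 2.2 and 2.3, with: *open-label to patient and treating practitioner; evaluator- and laboratory-blinded*.

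Under the second route, also:

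- have patients complete TNSS, VAS and RQLQ themselves;
- instruct them not to disclose their treatment to the evaluator;
- send sera for ELISA under a code that does not carry the group;
- state in the conclusions that patient-reported outcomes are unblinded.

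Recording the evaluator's guess of allocation at the last visit would be a useful check but is optional.

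The cost is a wording amendment, one instruction to patients and a sample-coding step. The downside is a less favourable design label. No dose, schedule or clinical rule is affected.
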